## Methods

### Setting

The main trial site is the Department of Anaesthesiology, Intensive Care Medicine, Emergency Therapy and Pain Therapy at the University Hospital of Wuerzburg. Further participating sites will be located at the departments of anaesthesiology of hospitals of primary and maximum care in Germany, Austria and Switzerland. Data collection will take place during the induction of anaesthesia prior to elective surgical procedures under general anaesthesia and, after the operation, in the peri-anaesthesiologic ward.

Inclusion criteria.Adult patientsScheduled for elective, non-cardiac surgical procedureNeed for endotracheal intubation as determined during the premedication visit

Care providers performing the intubation will have at least one year of training in anaesthesiology and sufficient experience in the use of all devices tested.

Exclusion criteria.Previous participation in this studyPregnancyNeed for fibreoptic intubationPatients scheduled for bariatric surgeryAny circumstance that will lead the anaesthesiologist(s) in charge to believe (before randomization)

That random assignment of a laryngoscopy instrument may compromise patient safety during induction of anaesthesia.

### Interventions

The preparations for induction of anaesthesia as well as establishing the necessary patient monitoring will take place in accordance with the stipulations of the anaesthetist in charge and with local standards. Randomization will take place electronically on the day of the intervention; the randomization result is communicated to the team performing the intervention (i.e. anaesthetist and anaesthesia nurse) in such a way that the patient is unaware of it. The study protocol does not specify the manufacturer or model of the laryngoscope to be used (e.g., disposable vs. reusable blades). However, the kind of blade will be recorded, as previous research suggested considerably reduced glottic view with (disposable) plastic blades compared with metal blades [26].

The choice and dosage of the anaesthetics as well as the sequence of administration is up to the decision of the anaesthetist in charge. For better comparability between the interventions, adequate pre-oxygenation (etO2 > 80%) and relaxation of the patient (ideally, train of four (TOF) = 0) is required before starting the laryngoscopy. The process of laryngoscopy (and thus also the first attempt at intubation) begins when the blade of the laryngoscope passes the patient’s row of teeth for the first time. The trial observer will also start the time measurement for the intubation procedure at this timepoint. The intubation is considered to have been completed successfully when the first capnographic end-expiratory CO2 detection is possible after the endotracheal tube has been placed. In the event of failure, the first attempt at intubation is deemed to have ended at the point in time when either the laryngoscope (e.g., after inadequate visibility of the vocal cords) or the endotracheal tube is removed from the patient’s mouth. Each additional intubation attempt using the same criteria should be considered a completed attempt.

The use of an intubation stylet is not primarily intended; the exception here is the use of a hyper-angulated blade, which cannot be used properly without a stylet. The routine use of a stylet for every endotracheal intubation is discussed in the literature in the context of critically ill patients [27], but ultimately does not reflect common practice in elective, peri-operative intubations. The use of a stylet after the start of the first intubation attempt with the other two types of blades is considered a change of device and thus also a failure of the first intubation attempt. If the anaesthetist in charge using a (video) laryngoscope with a Macintosh blade chooses to use a stylet for whatever reason before the start of the first attempt at intubation, this will be tolerated as per the study protocol.

After completion of the intervention, both the nurse and the anaesthetist in charge will answer the MHPTS questionnaire and the NASA-TLX questionnaire. To ensure that no necessary medical measures are delayed or hindered under any circumstances will be of the essence.

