### Choice of comparators

In this study, three different modalities of laryngoscopy for endotracheal intubation will be compared (s. Fig. 1): 1. conventional, direct laryngoscopy using a Macintosh blade. This procedure is considered the gold standard and is routinely used in the peri-operative setting as well as in intensive care and emergency medicine. 2. use of VAL with a Macintosh-shaped blade. By positioning the camera at the tip of the blade, the field of view onto the glottic plane is improved, as there is no need to establish a direct line of sight from the outside to the tracheal inlet (as is the case with conventional laryngoscopy). 3. use of VAL with a hyper-angulated blade. This shape of laryngoscope blade cannot be used in conventional, direct laryngoscopy because the strong curvature renders a direct line of view from the outside impossible due to the geometry of the instrument. So far, hyper-angulated blades are often used as a backup instrument when a view of the glottic plane cannot be achieved with the Macintosh blade due to anatomic abnormalities, even with a video-assisted laryngoscope. This often enables endotracheal intubation in patients who could otherwise not be intubated through conventional laryngoscopy. At the same time, however, it is conceivable that the rather extreme curvature of the blade may prove disadvantageous in individual cases compared with less curved blade variants. This may be because insertion of the tube is difficult due to the curvature of the blade and indirect vision, or because fluids like mucus or blood make it impossible to see through the video-optical system.

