### Outcomes

The primary endpoint is the rate of successful intubations at first attempt as a dichotomous (successful/unsuccessful) event. The first attempt starts with the laryngoscope blade passing the patient’s row of teeth. The attempt is considered unsuccessful if a complete retraction of the laryngoscope or the endotracheal tube from the oropharynx is necessary for any reason (need for bag ventilation, change of device, change of patient position, change in the curvature of the stylet, etc.). Manoeuvres that can be performed during laryngoscopy, such as BURP or reclining the head, which end with successful intubation, count towards the first attempt.

Secondary outcomes are as follows:

Parameters regarding the duration of the interventiontime to successful intubation (i.e. from start of first intubation attempt to first positive capnography via an endotracheal tube).time to first glottic view (as announced by the anaesthetist)Cormack & Lehane gradeIntubation success:total number of attemptsnumber of attempts using the randomized devicesuccess rate of intubation attempts regarding the respective deviceInfluence of the device on human factors during the interventionMayo High Performance Teamwork ScaleNASA-TLXComplications: occurrence of one or more of the followingDrop of SpO2 below 90%Regurgitation as announced by the anaesthetistNeed for bronchoscopy due to suspected aspirationDental injury or dental clicks upon contact with the bladeSoft tissue injuries as detected by blood on the bladeVisible swelling, bleeding or other injury of the lipsNeed for resuscitation (administration of adrenalin, chest compressions, defibrillation or any combination thereof)DeathOccurrence of any adverse event (AE) or serious adverse event (SAE)Need for auxiliary devices or switch of laryngoscopy deviceManoeuvres to optimize intubation conditions after the first attempt to intubate the patient has startedSwitch to alternate laryngoscopy deviceSwitch of the anaesthetistsSwitch of airway deviceRelevant vital parameters during the intervention: baseline SpO2 and lowest value during the airway procedurePost-operative sore throat, coughing or hoarseness: each rated from 0 to 3, score adapted from Park et al. [27]. This outcome will not be assessed in patients who continue to be invasively ventilated >2 hours after surgery.

Further patient-related parameters to be collected are:

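### A tube or blade withdrawn from the oropharynx but kept in the mouth is a failed first attempt under Outcomes, yet under Interventions that attempt never ended

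*Protocol article*

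**What the plan says.** Outcomes contains the success rule of the primary endpoint: "The attempt is considered unsuccessful if a complete retraction of the laryngoscope or the endotracheal tube from the oropharynx is necessary for any reason". The reasons it lists are "need for bag ventilation, change of device, change of patient position, change in the curvature of the stylet, etc". It also states what stays inside the attempt: "Manoeuvres that can be performed during laryngoscopy, such as BURP or reclining the head, which end with successful intubation, count towards the first attempt".

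Interventions deals with the end of an attempt. "In the event of failure, the first attempt at intubation is deemed to have ended at the point in time when either the laryngoscope" (an example of poor view follows) "or the endotracheal tube is removed from the patient’s mouth". It then extends the rule to later attempts: "Each additional intubation attempt using the same criteria should be considered a completed attempt". Both sections start the first attempt when the blade passes the row of teeth. Interventions completes the intubation when CO2 is first detected by capnography.

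On the hyper-angulated blade (H-VAL), Choice of comparators regards a disadvantage in individual cases as conceivable, one possible reason being that "insertion of the tube is difficult due to the curvature of the blade and indirect vision". Interventions does not primarily intend a stylet, but "the exception here is the use of a hyper-angulated blade, which cannot be used properly without a stylet".

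Blinding says that the observers cannot be blinded. Biometry has them record the data in real time. Setting plans several sites in three countries.

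**The concern.** The oropharynx lies behind the oral cavity, so a tube or blade can be wholly out of the one and still inside the other. The failure rule uses the first boundary, and the rule that ends and counts attempts uses the second. For an event between the two, an observer following both sections has no consistent entry to make.

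The event feeds the primary endpoint and three secondary outcomes: total number of attempts, number of attempts with the randomised device, and success rate by device. Time to intubation is not affected, because it runs from the start of the first attempt to first positive capnography. With unblinded observers coding live at several sites, the same event could be scored differently by site or by device. If such events were more frequent in one arm, the reading adopted would shift the between-arm difference that is compared with a 5-point margin.

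**Working it through.** **Step 1: the two rules applied to the same events.**

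| Event before CO2 detection | Outcomes: first attempt | Interventions: end and count | Do they fit? |
|---|---|---|---|
| Tube or blade taken out of the mouth | failed | attempt ended; a further try is counted | yes |
| Tube re-aimed without leaving the oropharynx | not failed | attempt continues | yes |
| Tube or blade fully out of the oropharynx, still in the mouth, then passed | failed | attempt not ended; no second attempt | no |
| Tube alone out of the mouth, blade left in place | failed | attempt ended, but the start rule (blade passing the teeth) cannot recur | start of next attempt undefined |

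In the third row, strict use of both sections records a failed first attempt, a total of one attempt, and a successful intubation. An observer who sees the inconsistency can resolve it as a success on attempt one or as a success on attempt two, and the text supports neither choice over the other.

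**Step 2: the sample size behind any illustration.** Sample size assumes 90% success in all arms, a 5% difference (read as percentage points), one-sided 2.5% per hypothesis, 90% power and an unpooled Z-test. Then

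n per arm = (1.960 + 1.282)² × 2 × 0.90 × 0.10 / 0.05² = 10.507 × 0.18 / 0.0025 = 756.5, so 757.

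The section prints 3 × 824 = 2526, but 3 × 824 = 2472 and 2526 / 3 = 842. A 10% allowance for dropout would give 757 / 0.90 = 841.1, so 842, but the article states no such allowance. I use 842 per arm as an inference from the printed total.

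**Step 3: illustration under an assumed shift.** The documents give no rate for the event in the third row. Suppose that x percentage points of attempts move from success to failure. With pC the success rate under conventional direct laryngoscopy (CDL) and pH that under H-VAL,

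SE = √{[pC(1 − pC) + pH(1 − pH)] / 842}

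power = Φ{[0.05 − (pC − pH)] / SE − 1.960}

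- H-VAL only, x = 1: SE = √[(0.0900 + 0.0979) / 842] = 0.01494; 0.04 / 0.01494 − 1.960 = 0.718; power 76.4%.
- All arms, x = 1: SE = √(2 × 0.0979 / 842) = 0.01525; 0.05 / 0.01525 − 1.960 = 1.319; power 90.6%.

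| x (points, assumed) | H-VAL only | All arms equally |
|---|---|---|
| 0 | 92.8% | 92.8% |
| 1 | 76.4% | 90.6% |
| 2 | 50.3% | 88.4% |
| 3 | 25.1% | 86.2% |

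With the printed 824 per arm, the H-VAL-only column is 92.3%, 75.5%, 49.5% and 24.6%, so the choice between 824 and 842 is immaterial here.

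**The case against.** The strongest reply is that the two sentences do different jobs. The one in Interventions is conditional on failure: it times the end of an attempt that has already failed, and Outcomes alone decides whether it failed. That is correct, and a reader might wrongly infer that the protocol states two competing failure rules. It does not remove the problem. Interventions applies the mouth criterion to counting later attempts as well, so even with Outcomes as the only failure rule, the count contradicts the failure.

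Second, the disputed event is narrow. Each reason that Outcomes names would normally bring the device or tube out of the mouth, where the sections agree, and a tube re-aimed within the oropharynx meets neither criterion. A complete retraction could also be read as removal from the mouth. This stands: re-aimed tubes in general are not affected. But the list is open-ended and the rule applies whatever the reason, so the reading is left to the observer.

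Third, a reader might infer that the cases fall mostly in the hyper-angulated arm and could decide the trial. The documents do not support this. Choice of comparators calls the insertion difficulty only conceivable, in individual cases, and names obscured optics as another possible reason. No frequency by arm is given. Design also describes a first stage with both video arms combined, where a shift in one arm would be diluted, while Statistical analysis tests each arm separately.

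Fourth, the article condenses a longer protocol and data forms that are not shown, where observer instructions may sit. That would excuse a missing detail. Here both rules are printed, and they do not fit together.

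**Conclusion.** The point holds in a limited form. For a tube or blade withdrawn completely from the oropharynx, kept inside the mouth and then passed, Outcomes and Interventions give a failed first attempt that never ended and was followed by no second attempt. The start of a new attempt is also undefined when only the tube was withdrawn. This concerns the primary endpoint and the attempt counts, coded live by unblinded observers, so it should be corrected.

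Its effect on the result cannot be quantified. Such events may be more frequent with the hyper-angulated blade, given the stylet and the possible insertion difficulty, but that is an inference without data. The power figures rest on an assumed shift, on 90% success otherwise, on an absolute 5-point margin and on the inferred 842 per arm. They show that the damage would come from differential coding: a loss from 92.8% to between 76.4% and 25.1% if 1 to 3 points moved in H-VAL alone, against 90.6% to 86.2% if all arms moved equally. They are not an estimate of what will happen.

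**What to change.** Before data are coded, the investigators should choose one landmark that a bystander can see and use it in both sections for first-attempt failure, end of attempt and attempt count. The row of teeth, which already defines the start, is one workable choice; which landmark to adopt is for the investigators to decide. The revised text should also:

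- say how re-aiming a tube or blade inside the mouth is scored;
- say when a new attempt starts if only the tube was withdrawn and the blade stayed in place;
- keep the two separate failure conditions, namely a stylet introduced after the start with either Macintosh-type blade (Interventions) and a departure from the allocated device between randomisation and the first attempt (Recruitment).

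The cost is protocol wording and observer training. No extra patients or data items are needed.

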### Outcomes

The primary endpoint is the rate of successful intubations at first attempt as a dichotomous (successful/unsuccessful) event. The first attempt starts with the laryngoscope blade passing the patient’s row of teeth. The attempt is considered unsuccessful if a complete retraction of the laryngoscope or the endotracheal tube from the oropharynx is necessary for any reason (need for bag ventilation, change of device, change of patient position, change in the curvature of the stylet, etc.). Manoeuvres that can be performed during laryngoscopy, such as BURP or reclining the head, which end with successful intubation, count towards the first attempt.

Secondary outcomes are as follows:

Parameters regarding the duration of the interventiontime to successful intubation (i.e. from start of first intubation attempt to first positive capnography via an endotracheal tube).time to first glottic view (as announced by the anaesthetist)Cormack & Lehane gradeIntubation success:total number of attemptsnumber of attempts using the randomized devicesuccess rate of intubation attempts regarding the respective deviceInfluence of the device on human factors during the interventionMayo High Performance Teamwork ScaleNASA-TLXComplications: occurrence of one or more of the followingDrop of SpO2 below 90%Regurgitation as announced by the anaesthetistNeed for bronchoscopy due to suspected aspirationDental injury or dental clicks upon contact with the bladeSoft tissue injuries as detected by blood on the bladeVisible swelling, bleeding or other injury of the lipsNeed for resuscitation (administration of adrenalin, chest compressions, defibrillation or any combination thereof)DeathOccurrence of any adverse event (AE) or serious adverse event (SAE)Need for auxiliary devices or switch of laryngoscopy deviceManoeuvres to optimize intubation conditions after the first attempt to intubate the patient has startedSwitch to alternate laryngoscopy deviceSwitch of the anaesthetistsSwitch of airway deviceRelevant vital parameters during the intervention: baseline SpO2 and lowest value during the airway procedurePost-operative sore throat, coughing or hoarseness: each rated from 0 to 3, score adapted from Park et al. [27]. This outcome will not be assessed in patients who continue to be invasively ventilated >2 hours after surgery.

Further patient-related parameters to be collected are:

AgeGenderHeight and weightASA classificationMallampati scoreupper lip bite test (ULBT) classification

Where applicable, these can be obtained from the patient’s chart.

Care provider-related data to be collected are:

Job experience (years; anaesthetist only)

The observable outcomes will in part be captured using the Work Observation Method By Activity Timing (WOMBAT) software (WOMBAT 3.0, 2020) [28].

Schedule of activities.

See Table. 1

**Table 1 Tab1:** Schedule of activities

	Screening	randomization	intervention	post-intervention	follow-up
	up to 14 days prior to intervention	day 0 briefly before intervention	day 0	day 0 immediately after intervention	day 0 2 h (± 30 min) after extubation
visit	V1	V2	V3	V4	V5
inclusion criteria	X				
exclusion criteria	X				
informed consent	X				
registration	X				
sociodemographics, medical history	X				
acute medical concerns by responsible anaesthetist preventing randomization		X			
randomization		X			
experience of *anaesthetist*			X		
upper lip bite test, Mallampati score	X		(X)^a^		
pre-oxygenation (> 80% etO_2_), relaxation (TOF = 0)			X		
intubation (incl. number of attempts and time to intubation)			X		
Cormack-Lehane grade			X		
switch of device or provider			X		
vital signs			X		
injuries			X		
Mayo High Performance Teamwork scale				X	
NASA-TLX				X	
sore throat, coughing, hoarseness					X

^a^ if these parameters cannot be obtained from the patient’s chart, they will be obtained by the observer prior to the intervention

### Sample size

The estimation of the appropriate sample size is based on the corresponding Null hypotheses of the primary hypothesis, i.e. the assumption that VAL is inferior to conventional laryngoscopy in terms of first-attempt success rate, irrespective of the kind of blade in use. From clinical experience and previously published data, we assume an a-priori success rate of 90% across all groups. A clinically relevant difference between groups in this context is suggested at 5%, as is the accepted overall type-I error. Given that both Null hypotheses will be tested separately, the type-I error limit in each case is 2.5%. The desired statistical power is set to 90%. The Null hypotheses will be tested for non-inferiority using a one-sided Z test with unpooled variance. Based on these assumptions, the required sample size amounts to 3 * 824 = 2526 participants.

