## Methods and design

### Design

This is a randomized controlled multi-centre study with a three-arm parallel study design (s. Fig. 2). The primary endpoint is the successful placement of the endo- tracheal tube at first attempt (success at first attempt) as a dichotomous feature. The patients included in the study will be evenly distributed across the three study arms (1:1:1). The underlying approach is the premise of non-inferiority of the experimental interventions compared to the established standard procedure.

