### Statistical analysis

The primary outcome is the rate of successful intubations at first attempt as a fraction of dichotomous events. In a first analysis step we test the hypothesis, that neither video assisted laryngoscopy with a Macintosh-shaped blade (M-VAL) nor video assisted laryngoscopy with a hyper-angulated blade (H-VAL) are inferior to conventional direct laryngoscopy (CDL) with regard to the primary outcome. In terms of the statistics, this corresponds to testing the Null hypothesis that at least one of the interventions M-VAL or H-VAL is inferior to CDL. Both Null hypotheses will be tested for separately. The overall type-I error will be set to 5%. Thus, both Null hypotheses will be tested on a local significance level of 0.025 using a one-sided Z-test with unpooled variance. Non-inferiority is defined as described in subsection “sample size”.

Only if both Null hypotheses can be rejected will there be a second analysis step where the single interventions M-VAL and H-VAL will be tested pairwise for superiority using a two-sided Z-test with unpooled variance. As we apply the principle of fixed sequence hierarchical testing, this analysis can be performed at a local significance level of 0.05 to meet the family-wise error rate of 0.05.

A planned interim analysis will be conducted after 200 randomized interventions. This will first and foremost happen to review feasibility and data quality before expanding to additional study sites. We do not foresee any substantial safety concerns in this trial which would need to be assessed at this stage.

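### The sample-size sentence is wrong as printed: 3 × 824 is 2472, not 2526, and the listed assumptions give 757 per arm, so neither 824 nor the 842 implied by the total can be reproduced

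*Protocol article*

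**What the plan says.** The Sample size section of the protocol article lists every input that a non-inferiority calculation for two proportions needs:

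- Success rate: "we assume an a-priori success rate of 90% across all groups".
- Margin, in per cent: "A clinically relevant difference between groups in this context is suggested at 5".
- Type-I error, in per cent: "the type-I error limit in each case is 2.5".
- Power, in per cent: "The desired statistical power is set to 90".
- Test: "The Null hypotheses will be tested for non-inferiority using a one-sided Z test with unpooled variance".

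It then concludes: "Based on these assumptions, the required sample size amounts to 3 * 824 = 2526 participants".

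The Statistical analysis section repeats the test and its level: "both Null hypotheses will be tested on a local significance level of 0.025 using a one-sided Z-test with unpooled variance". The Design section says that patients are "evenly distributed across the three study arms (1:1:1"). The Abstract and the Discussion both put recruitment above 2500. No allowance for dropout or non-evaluable patients is stated.

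**The concern.** The two sides of the printed equation disagree by 54 patients, or 18 per arm, so at least one number is wrong. Correcting the multiplication does not settle the matter, because neither 824 nor 842 per arm comes out of the assumptions to which the sentence attributes the result.

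This is the only place where the article gives an exact target, overall or per arm. The final report will be measured against it. The Discussion also relies on the calculation when it argues that no earlier trial was large enough. A reader who tries to verify it cannot, and cannot tell what the patients beyond the computed requirement are for.

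**Working it through.** **Step 1: the printed product.** 3 × 824 = 2472, and 2526 − 2472 = 54. Working back from the total, 2526 / 3 = 842, which is 824 with its last two digits exchanged. The goal of over 2500 fits 2526 and excludes 2472.

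**Step 2: the size from the listed inputs.** With p = 0.90 in both arms, true difference 0, margin 0.05, one-sided 0.025 (z = 1.960), power 90% (z = 1.282), unpooled variance and equal arms:

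n = [p(1 − p) + p(1 − p)] × (1.960 + 1.282)² / 0.05² = 0.18 × (1.960 + 1.282)² / 0.0025 = 756.5

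Rounded up, this is 757 per arm, and 3 × 757 = 2271. The printed 824 is 67 per arm (8.9%) above this. The implied 842 is 85 per arm (11.2%) above it, or 255 patients in total. These gaps are too large for rounding.

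**Step 3: other readings of the inputs.** Each row changes one element.

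| Change | n per arm |
|---|---|
| One-sided 0.05 | 617 |
| One-sided 0.0125 | 894 |
| Power 80% | 566 |
| Power 95% | 936 |
| Continuity correction | 797 |
| Unpooled variance at 90% and 85% | 915 |
| Pooled two-proportion formula, 90% v 85% | 918 |
| Both video arms combined against control (2:1) | 568 |
| 90% power to reject both nulls, correlation 0.5 | about 901 |
| 90% power to reject both nulls, independent tests | about 929 |

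None gives 824 or 842.

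**Step 4: inflation.** Dividing by the retained fraction, 757 / 0.90 = 841.1, rounded up to 842, and 3 × 842 = 2526. This matches the printed total exactly, but it depends on rounding to 757 first: 756.5 / 0.90 = 840.6 gives 841 and 2523. Multiplying instead, 757 × 1.10 = 832.7 gives 833 and 2499. To reach 824 by division would need an allowance of about 8.1%.

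**Step 5: power at each size.** Power per comparison is Φ(0.05 / √(0.18 / n) − 1.960). The Statistical analysis section allows the superiority step only if both nulls are rejected, so the joint figure is shown too. It uses a bivariate normal with correlation 0.5, which follows from the shared control arm when arms and success rates are equal.

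| n per arm | One comparison | Both nulls rejected |
|---|---|---|
| 757 | 90.0% | about 83% |
| 824 | 92.3% | about 87% |
| 842 | 92.8% | about 88% |

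**The case against.** The strongest reply is that nothing important turns on the slip. The recruitment goal elsewhere in the article shows which side of the equation is right. Both 824 and 842 exceed 757, so each comparison has more than the desired 90% power. The article also condenses a German-language protocol that is not shown, and a loss allowance may well be stated there. Most of this stands. The absence of a dropout percentage from an article is not in itself a fault. What remains is narrower: the sentence says that the total follows from the assumptions just listed, and it does not.

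Three stronger readings are tempting, and the document does not support them:

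- A reader might infer that the trial could stop at either 2472 or 2526, or that randomisation lists are affected. The goal of over 2500 rules out 2472. The Recruitment section describes online, computer-generated allocation, with no list length or site quota tied to this number.
- A reader might infer that the trial is underpowered. For a single comparison it is not, at either figure.
- A reader might infer that the 255 patients above 2271 are surplus. Both nulls must be rejected before the second step, and at 757 per arm the chance of that is only about 83%.

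The 10% allowance should also be held loosely. The Recruitment section expects no substantial adherence problems, and it counts a switch away from the allocated device before the first attempt as a failure, so such patients stay evaluable. Nothing in the text points to a tenth being lost.

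**Conclusion.** The point holds as an error of correctness and reproducibility. The equation is false by 54 patients. The listed inputs give 757 per arm (2271), against 842 per arm implied by the total (2526). That 824 is a misprint of 842 is probable, given the recruitment goal and the exchanged digits. That a 10% inflation explains the step from 757 to 842 is plausible but unconfirmed.

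The power figures rest on the protocol's own assumption of 90% success in all arms with no true difference. The joint figures also assume correlation 0.5. The intended total and the analysis are not called into question.

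**What to change.** Correct the sentence in the Sample size section so that it:

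1. gives 757 per arm (2271 in total) as the result of the listed inputs;
2. confirms 3 × 842 = 2526 as the number to be randomised, if that is what was intended;
3. names the inflation that links 757 to 842. If it was 10% for non-evaluable patients, a suitable wording is: the listed assumptions require 757 evaluable patients per arm; allowing for 10% non-evaluable, 842 per arm, 2526 in total, are randomised.

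If no inflation was used, keep 2526 and replace the 90% by the power that this size gives: 92.8% per comparison and about 88% for rejecting both nulls, with the assumed correlation of 0.5 stated. Giving 757 alone as the requirement would mislead, because it hides the joint power of about 83% at that size.

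The cost is a short correction to one sentence. It needs no extra patients and no change to the design or the analysis.
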